|  | Study informed consent |  | X |  |  |  |
|  |  |  |  |  |  |  |
| **II. Enrollment & Study ID** | Study ID number assignment |  | X |  |  |  |
|  | Patient registration in Register |  | X |  |  |  |
|  | Patient file creation |  | X |  |  |  |
|  | Patient appointment card |  | X |  |  |  |
|  |  |  |  |  |  |  |
| **III. Physical Measurements** | Height |  | X |  |  |  |
|  | Weight |  | X | X | X | X |
|  | Waist circumference |  | X |  | X | X |
|  | Blood pressure |  | X | X | X | X |
|  | 7-day pedometer steps |  | X |  |  | X |
|  |  |  |  |  |  |  |
| **IV. Biochemical** | FPG (Uganda & South Africa) | X, X | X | X | X | X |
|  | HbA1c (All sites) |  | X |  |  | X |
|  |  |  |  |  |  |  |
| **V. Basic participant data** | Pre-eligibility assessment | X |  |  |  |  |
|  | Eligibility confirmation |  | X |  |  |  |
|  | Eligibility and recruitment check |  | X |  |  |  |
|  | Contact Information |  | X |  |  |  |
|  | Demographic and social measures |  | X |  |  |  |
|  | Medical and medication history |  | X |  |  |  |
|  | Behavioral measures (diet, physical activity, foot care, tobacco use, alcohol consumption) |  | X |  |  | X |
|  |  |  |  |  |  |  |
| **VI. Intervention process measures** | Participant diabetes knowledge |  | X |  |  | X |
|  | Illness perception |  | X |  |  | X |
|  | Social support and sources of support |  | X |  |  | X |
|  | Self-efficacy, autonomy support & self-regulation |  | X |  |  | X |
|  | Psychological adjustment |  | X |  |  | X |
|  | Quality of life & Stress |  | X |  |  | X |
|  | Diabetes treatment satisfaction |  |  |  |  | X |
|  | Out of pocket expenditure |  |  | X | X | X |
|  | Incremental cost to the health facility |  |  | X | X | X |
|  | Adherence to study procedures and to intervention elements |  | X |  |  | X |
|  |  |  |  |  |  |  |
| **VII. Facility forms** | Process evaluation |  |  | X | X | X |
|  |  |  |  |  |  |  |
| **VIII. Community forms** | Environment context measurement (EPOC) |  | X |  |  |  |

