## 3.13 Statistical analysis Plan

### 3.13.1 Primary intervention efficacy analysis:

We will use intention-to-treat analyses for all primary outcomes, that is, all participants will be analyzed as assigned to their respective study arms. Since the unit of analysis for the primary outcome of interest are the individual participants, to minimize the effect of within cluster correlations, we will employ generalized estimating equations (GEEs) to evaluate changes over time in HbA1c values as a continuous variable among participants with pre-diabetes; and the proportion of participants with stabilized plasma glucose among participants with diabetes, in relation to assigned trial arm. Thus we use multivariable linear regression mixed effects modeling with a random intercept, unstructured correlation matrix and robust standard errors, to evaluate changes over time in HbA1c, and logistic regression analysis to compare the proportion of participants with stabilized plasma glucose among participants with diabetes.

Missing data are expected due to missed appointments, drop-outs, loss-to-follow-up and/or death. One technique to deal with missing data when the outcome is continuous, is hierarchical linear modeling (HLM; also called random effects regression) [Singer et al. 2003].

We do not anticipate differences in the intercept within each site, as randomization is expected to balance out baseline differences between the groups. However, there may be differences in the intercepts between sites, reflecting differences within the client populations in each site. We anticipate that the primary factor affecting the slope (i.e., the rate of change of the outcome measure) will be group membership (i.e, facility only or facility plus community intervention). If there is any significant unexplained variance after baseline differences and site membership have been accounted for, we can look for other factors influencing the slope, such as sex, age, co-morbidities, etc. Another analytic option that will be considered is generalized estimating equations (GEE) [Zeger et al. 1986], which can adjust for clustered, serially correlated data with missing values. The choice of techniques will be based on the nature of the data.

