5. Similarly, for the degree of implementation of the intervention elements in each country, and differences between the country sites, we will compare the process evaluation variables/ indicators regarding ways in which program services and goods are provided (i.e. deviations) using the t-test statistic or the equivalent non-parametric test. For categorical context variables we will use the chi-square test statistic.
6. To compare changes in participant perceptions towards diabetes, physical activity, dietary behavior; and changes within contexts, as a result of implementing the intervention elements; we use multivariable linear regression mixed effects modeling with a random intercept, unstructured correlation matrix and robust standard errors, to evaluate changes over time in these outcomes of interest in relation to the assigned study arm. Visit month (categorical) at which the outcome is measured, study arm would be included in the model as fixed effects. The null hypothesis to be tested in this analysis would be that the mean changes at all the post-baseline visit months are equal between the treatment groups. The alternative hypothesis would be that the mean changes are not equal at, at least one post-baseline visit month.

We recognize that since sample size calculations for this trial were not based on the secondary outcomes, lack of significant differences in analysis of secondary outcomes might either be true lack of differences in these outcomes, or due to the fact that the trial was not sufficiently powered to detect differences in these outcomes. Thus interpretation of findings on secondary outcomes will be done with caution in case we do not detect any differences.

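### The model for perceptions, diet and physical activity lists visit and arm but no arm-by-visit term, so nothing in it tests the stated null of equal mean changes

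*Protocol*

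**What the plan says.** Item 6 of section 3.13.2 covers the comparison of changes in perceptions, physical activity and dietary behaviour, which serves secondary objective 4 in section 2.2.2.

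- **Model:** "multivariable linear regression mixed effects modeling with a random intercept, unstructured correlation matrix and robust standard errors".
- **Aim:** "to evaluate changes over time in these outcomes of interest in relation to the assigned study arm".
- **Fixed effects:** "Visit month (categorical) at which the outcome is measured, study arm would be included in the model as fixed effects". No interaction, baseline covariate or change-score response is named.
- **Null:** "the mean changes at all the post-baseline visit months are equal between the treatment groups".
- **Alternative:** "the mean changes are not equal at, at least one post-baseline visit month".

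Table 15 in section 3.8 schedules these outcomes at baseline and month 12, with nothing at months 3 or 6. The row for illness perception reads "Illness perception | | X | | | X" (columns: screening, baseline, M3, M6, M12), and the row for behavioural measures has the same pattern. The tables at the head of Parts I and II of the data collection tools also give diet, physical activity and the process measures at baseline and end-line only.

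The closing paragraph of section 3.13.2 says that the sample size was not based on secondary outcomes.

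**The concern.** The hypothesis is about differences in change, but the listed terms contain no difference in change. A model with visit and arm alone gives one arm difference that applies at every visit, baseline included. An analyst who fits the listed terms and reads off the arm coefficient would report an average level difference as though it answered the question about change.

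Two things follow. A real intervention effect is diluted, because the visit at which no effect can yet exist counts equally with month 12. And a difference between arms that was present before the intervention is reported as part of its effect. The second matters in a trial that randomises few units: section 3.10 gives 9 clusters in Uganda, 4 in Sweden and 2 in South Africa.

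**Working it through.** The protocol gives no power or error rate for this analysis, so there is no figure to reproduce. The check is algebra, followed by an illustration on assumed values.

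**1. What the listed model estimates.** Let b0 be the arm difference at baseline and δ the difference in mean change, so the arm difference at month 12 is b0 + δ.

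- Visit + arm: the fitted arm difference is the same at both visits, so δ is fixed at zero. With two complete visits and equal variances, the arm coefficient is [b0 + (b0 + δ)]/2 = b0 + δ/2.
- Visit + arm + arm × visit: the interaction coefficient is δ, the quantity in the stated null.

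Hence:
- b0 = 0 gives δ/2, half the effect.
- δ = 0 gives b0, a baseline difference and nothing else.
- b0 = −0.1 SD with δ = 0.2 SD gives −0.1 + 0.1 = 0, so a real difference in change is hidden.

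A random-intercept model fitted to one simulated data set (5,000 per arm, δ = 0.40, b0 = 0, correlation 0.5) gave an arm coefficient of 0.197 without the interaction and an interaction coefficient of 0.407 with it. With unequal variances or missing visits the weights move away from one half, but the coefficient is still a weighted average that includes baseline.

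**2. Illustration of power.** Assumptions not in the protocol: outcome SD 1, true month 12 effect 0.25 SD, within-person correlation ρ of 0.3 to 0.7, no clustering, two-sided 5%. For n I took 240 per arm, the Ugandan figures in Tables 16(a) and 16(b) before allowance for loss to follow-up (112 + 128).

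- Arm term: estimate 0.125, SE = √((1 + ρ)/n).
- Arm × visit: estimate 0.25, SE = √(4(1 − ρ)/n).
- Month 12 adjusted for baseline: estimate 0.25, SE = √(2(1 − ρ²)/n).

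| ρ | Arm term: SE, z, power | Arm × visit: SE, z, power | Baseline-adjusted: SE, z, power |
|---|---|---|---|
| 0.3 | 0.0736, 1.70, 40% | 0.1080, 2.31, 64% | 0.0871, 2.87, 82% |
| 0.5 | 0.0791, 1.58, 35% | 0.0913, 2.74, 78% | 0.0791, 3.16, 89% |
| 0.7 | 0.0842, 1.49, 32% | 0.0707, 3.54, 94% | 0.0652, 3.83, 97% |

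Power is Φ(z − 1.96); the other tail is negligible. Simulation agrees to within about one percentage point.

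**3. Illustration of a baseline gap.** Take equal changes (δ = 0) and an imposed gap b0 = 0.2 SD.

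- Arm term: z = 0.2/SE = 2.72, 2.53 and 2.38 at ρ = 0.3, 0.5 and 0.7, so it rejects 78%, 72% and 66% of the time.
- Arm × visit: about 5%.
- Baseline-adjusted: the expected estimate is 0.2(1 − ρ), or 0.14, 0.10 and 0.06. It rejects 36%, 24% and 15% of the time.

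These rates are conditional on the gap. Without clustering, a 0.2 SD gap is 0.2/√(2/240) = 2.19 standard errors, which is exceeded in either direction in about 3% of randomisations. With no true gap, both the arm term and the interaction reject at about 5 to 6%.

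Clustering lowers the conditional rate if the standard error reflects it. Assume 3 facilities per Ugandan arm, ICC 0.05 and ρ = 0.5. The variance of a person's mean over two visits is (1 + 0.5)/2 = 0.75, so SE = √(2[0.05/3 + 0.70/240]) = 0.198, z = 1.01, and the arm term rejects about 17% of the time for the same gap.

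**The case against.** **Item 6 may be incomplete shorthand.** It says that these terms would be included, not that they are the only ones, and it never says that the arm coefficient is the test. The stated null and alternative are those of a joint arm-by-visit test, and the aim speaks of change over time in relation to arm. Section 3.13.1 uses the same model wording for HbA1c and expects that "the primary factor affecting the slope (i.e., the rate of change of the outcome measure) will be group membership". All of this suggests that an interaction was meant. It does not remove the conflict, because the only fixed effects named cannot test the hypothesis named. Nor can the point be left to an unseen analysis plan, since the protocol fixes both the terms and the hypothesis. It does bar the inference that the authors chose the arm main effect as their test. And since section 3.13.1 lists no interaction either, it shows intent rather than a correct model from which item 6 departs.

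**The response may be change from baseline.** With a single post-baseline visit, the arm term would then test exactly the stated null. But the text does not define the response that way, and on that reading a categorical visit factor would have no role. If there were several post-baseline visits, one arm term would test a common shift rather than a difference at one or more of them.

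**The numbers can be over-read.** A reader might take the 66 to 78% rejection as the trial's type I error. The documents do not support that: it depends on an imposed gap and ignores clustering. A reader might also say that the arm term loses most of its power. At correlation 0.3 it falls from 64% to 40%, a loss of under two-fifths; only at higher correlation is the loss larger than half.

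**Conclusion.** The point stands as a mismatch between model and hypothesis within one item. As listed, the model fixes the difference in change at zero, so no parameter in it tests the stated null. That part is algebra and needs no assumed SD, correlation or sample size. That the arm coefficient is the plain average of the baseline and month 12 differences, with a true effect halved, also requires complete data and equal variances.

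The power comparison (about 32 to 40% against 64 to 94%) is illustrative and rests on the assumptions listed in the working. The rejection rates for a 0.2 SD gap show the mechanism and are not an error rate for this trial.

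The affected outcomes are secondary and not powered, so the primary HbA1c conclusions are untouched. The correction should still be made. The caution at the end of section 3.13.2 concerns only findings of no difference, and gives no protection against a baseline difference read as an effect.

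**What to change.** In item 6, give the fixed effects as visit month, study arm and study arm by visit month. Name the arm-by-visit contrast at month 12 as the test of the stated null, with a joint test over visits for any outcome that has more than one post-baseline visit.

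An alternative for tools used only at baseline and month 12 is to model the month 12 value on arm and the baseline value. It is usually more precise, as the table in the working shows. It is not equivalent, however: it estimates the difference at month 12 given baseline, and can reject when mean changes are equal but baselines differ. If it is preferred, reword the null to match.

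The cost is one or two sentences of analysis text and one extra model term, with no new data.

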## 3.14 Ethical Considerations

Approval for conduct of this trial will be sought, and research ethical oversight provided by the Institutional Review Boards (IRB) at the respective trial sites; that is, the Higher Degrees, Research and Ethics Committee (HDREC) of Makerere University School of Public Health in Uganda, the Senate Research Committee of the University of the Western Cape in South Africa, and the Regional Ethical Board in Stockholm, in Sweden. In Uganda, further approval will be sought from the Uganda National Council for Science and Technology (UNCST).

We will seek written informed consent, making sure that each eligible subject understands that participation in the trial is voluntary, and that he/she may withdraw participation at any time, even after consent is granted. Thus Field Research Assistants (FRA) will review to eligible subjects, the trial objectives, procedures and expectations of the trial from any enrolled participant; prior to enrollment in the trial. Eligible subjects will then be provided with the opportunity to voluntarily decide whether to provide consent to participate or not. The consent process will be completed with the subject providing their signature, or a witnessed thumb-print on the consent document.

To ensure confidentiality of trial participant data, completed data tools will only bear the participant study number (no names or locator information), and will only be handled by authorized study personnel. The names of participants will only appear on the consent documents, and their locator information on the Contact Informtion form. These participant identifying documents will be stored separately from the rest of the databases. All data forms will be kept in a lockable office space/drawer that is accessible to only authorized trial supervisors and project coordinators at each respective trial site.

# 5.0 APPENDICES

## 5,1 Planned Timeline

|  | **2016** | | | | | | | | | | | | **2017** | | | | | | | | | | | | **2018** | | | | | | | | | | | | **2019** | | | | | |
| --- | --- | --- | --- | --- | --- | --- | --- | --- | --- | --- | --- | --- | --- | --- | --- | --- | --- | --- | --- | --- | --- | --- | --- | --- | --- | --- | --- | --- | --- | --- | --- | --- | --- | --- | --- | --- | --- | --- | --- | --- | --- | --- |
|  | J | F | M | A | M | J | J | A | S | O | N | D | J | F | M | A | M | J | J | A | S | O | N | D | J | F | M | A | M | J | J | A | S | O | N | D | J | F | M | A | M | J |
| Trial proposal development | X | X | X | X |  |  |  |  |  |  |  |  |  |  |  |  |  |  |  |  |  |  |  |  |  |  |  |  |  |  |  |  |  |  |  |  |  |  |  |  |  |  |
| Data collection tools and guidelines development |  | X | X | X | X | X |  |  |  |  |  |  |  |  |  |  |  |  |  |  |  |  |  |  |  |  |  |  |  |  |  |  |  |  |  |  |  |  |  |  |  |  |
| Site-specific additions/modifications to the proposal |  |  |  |  | X | X |  |  |  |  |  |  |  |  |  |  |  |  |  |  |  |  |  |  |  |  |  |  |  |  |  |  |  |  |  |  |  |  |  |  |  |  |
| Acquire equipment, print tools, etc |  |  |  |  |  | X | X | X | X |  |  |  |  |  |  |  |  |  |  |  |  |  |  |  |  |  |  |  |  |  |  |  |  |  |  |  |  |  |  |  |  |  |
| Ethical approval processes |  |  |  |  |  |  | X | X | X |  |  |  |  |  |  |  |  |  |  |  |  |  |  |  |  |  |  |  |  |  |  |  |  |  |  |  |  |  |  |  |  |  |
| Community sensitization |  |  |  |  |  |  | X | X | X |  |  |  |  |  |  |  |  |  |  |  |  |  |  |  |  |  |  |  |  |  |  |  |  |  |  |  |  |  |  |  |  |  |
| Hire field personnel |  |  |  |  |  | X | X | X |  |  |  |  |  |  |  |  |  |  |  |  |  |  |  |  |  |  |  |  |  |  |  |  |  |  |  |  |  |  |  |  |  |  |
| Pre-test tools and guidelines |  |  |  |  |  |  | X | X |  |  |  |  |  |  |  |  |  |  |  |  |  |  |  |  |  |  |  |  |  |  |  |  |  |  |  |  |  |  |  |  |  |  |
| Database structure dev't |  |  |  |  |  |  | X | X | X |  |  |  |  |  |  |  |  |  |  |  |  |  |  |  |  |  |  |  |  |  |  |  |  |  |  |  |  |  |  |  |  |  |
| Training of study staff |  |  |  |  |  |  |  | X | X |  |  |  |  |  |  |  |  |  |  |  |  |  |  |  |  |  |  |  |  |  |  |  |  |  |  |  |  |  |  |  |  |  |
| Pilot implementation of intervention |  |  |  |  |  |  |  |  |  | X |  |  |  |  |  |  |  |  |  |  |  |  |  |  |  |  |  |  |  |  |  |  |  |  |  |  |  |  |  |  |  |  |
| Do necessary adjustment to the intervention |  |  |  |  |  |  |  |  |  |  | X | X |  |  |  |  |  |  |  |  |  |  |  |  |  |  |  |  |  |  |  |  |  |  |  |  |  |  |  |  |  |  |
| Enrollment into main trial |  |  |  |  |  |  |  |  |  |  |  |  | X | X | X | X | X | X | X | X | X | X | X |  |  |  |  |  |  |  |  |  |  |  |  |  |  |  |  |  |  |  |
| Follow-up |  |  |  |  |  |  |  |  |  |  |  |  | X | X | X | X | X | X | X | X | X | X | X | X | X | X | X | X | X | X | X | X | X | X | X | X |  |  |  |  |  |  |
| Data entry |  |  |  |  |  |  |  |  |  |  |  |  | X | X | X | X | X | X | X | X | X | X | X | X | X | X | X | X | X | X | X | X | X | X | X | X | X |  |  |  |  |  |
| Data cleaning |  |  |  |  |  |  |  |  |  |  |  |  |  | X | X | X | X | X | X | X | X | X | X | X | X | X | X | X | X | X | X | X | X | X | X | X | X |  |  |  |  |  |
| Preliminary report writing |  |  |  |  |  |  |  |  |  |  |  |  |  |  |  |  |  |  |  |  |  |  |  |  |  |  |  |  |  |  | X | X | X | X | X | X |  |  |  |  |  |  |
| Merging data from sites |  |  |  |  |  |  |  |  |  |  |  |  |  |  |  |  |  |  |  |  |  |  |  |  |  |  |  |  |  |  |  | X |  |  |  |  |  |  |  |  |  |  |
| Data analysis |  |  |  |  |  |  |  |  |  |  |  |  |  |  |  |  |  |  |  |  |  |  |  |  |  |  |  |  |  |  |  |  |  |  |  |  | X | X | X |  |  |  |
| Final report writing |  |  |  |  |  |  |  |  |  |  |  |  |  |  |  |  |  |  |  |  |  |  |  |  |  |  |  |  |  |  |  |  |  |  |  |  |  | X | X | X |  |  |
|  |  |  |  |  |  |  |  |  |  |  |  |  |  |  |  |  |  |  |  |  |  |  |  |  |  |  |  |  |  |  |  |  |  |  |  |  |  |  |  |  |  |  |

5.2: Care companion guidelines

1. **RECRUITMENT GUIDELINES**

**Recruitment of care companions screening (*to be answered by the patient*)(**[**Knowlton 2003**](#_ENREF_1)**)**

1. Who would you prefer to help you out if you needed help? E.g if you couldn’t take care of yourself, who would you want to stay with?
2. Who do you think will be the most helpful person in your life in dealing with Diabetes/prediabetes?
3. Is there anyone else who would be especially helpful with dealing with diabetes/prediabetes?

**Criteria for selection (*information for clinicians*)(**[**Nachega, Chaisson et al. 2010**](#_ENREF_3)**,** [**Kunutsor, Walley et al. 2011**](#_ENREF_2)**)**

1. Must be living in the patients’ household/neighborhood
2. Aware of patients’ health condition
3. Has accepted patients’ health condition and is a confidant
4. Willing and committed to support patient with care for a long period of time
5. **ROLE OF CARE COMPANIIONS**
6. Remind patients to go for next clinic appointments and peer group sessions.
7. Remind patients to take diabetes medication; observe and record while patient takes at least one dose per day?([Nachega, Chaisson et al. 2010](#_ENREF_3)).
8. Observe and confirm that daily/weekly physical activity goals are met.
9. Ensure a healthy diet for the patient.
10. **TRAINING GUIDELINES**

Patients and their selected care companions will undergo 90 minutes of baseline training on;

1. Diabetes/ prediabetes (causes, diagnosis, signs and symptoms, treatment and control)
2. Diabetes/prediabetes lifestyle (physical activity, diet)
3. Role of care companions

Care companions will receive booster health education every 3 months

| **Changes from previous version (from version 4.0)**  All changes highlighted in yellow in the document | **ALL PARTS**   1. All variables that have “yes” or “no” answers have been coded as:   Yes = 1  No = 0   1. All variables that use “Don’t know/don’t remember”, “Not applicable” or “Refused to answer” have been coded as:   Don’t know or don’t remember = 777  Not applicable = 888  Refused to answer = 999  **PART I**   1. New variable (study_id) added for screening ID before Step 1, ***only for sites using Redcap for data collection*** 2. Instruction variable (Inst_eli_1) added after Step 1 if eli_1=no 3. REDCAP USERS: STEP 2 d: third option (“participant has pre-diabetes”) added, and instruction text for data collectors (“For interviewers: If the participant has pre-diabetes, mark the selection ‘Participant has pre-diabetes’”) 4. REDCAP USERS: STEP 2 e: third option (“participant is male”) added, and instruction text for data collectors (“For interviewers: If the participant is male, mark the selection ‘Participant is male’”) 5. Instruction variable (inst_eli_2) added after Step 2 h if all Step 2 1-h are marked no 6. Section 3 d: dem_1d_other changed to “If 9, specify:” 7. Variable (inst_dem_1f_opt) added to choose option for reporting household income. Option 1=salary per day * number of days of work per month, Option 2=salary per month 8. REDCAP USERS: Note that variables dem_1f1 and dem_1f2 must be calculated by hand 9. Section 5: Instruction variable (inst_diet1) added at start 10. Section 5: The wording “How many servings of ____ do you eat on a typical day?” has been added to each food option (e.g. whole fruit, cut fruit, etc.). Applies to the following variables:     1. Diet_1b1-4     2. Diet_1d1-4     3. Diet_1h1-2     4. Diet_1j1-2 11. Instruction variable (inst_diet3) added after Section 5 p. 12. Section 5 t: 13. Start of diet_1t1a (“How many servings of sweetened, non-carbonated drinks…”) has been split from the question into a new instruction variable (inst_diet2a) 14. Diet_1t1a-f have been changed to “Number of Showcard 5.__ drinks consumed” 15. New variables added (diet_1t1a_total to diet_1t1f_total) to calculate total in mL: “Amount in mL of Showcard 5.___ drinks consumed:” (**Note. In Redcap, the calculation will be automatic) 16. Start of diet_1t2a (“How many servings of sugar-sweeteened fizzy drinks…”) has been split from the question into a new instruction variable (inst_diet2b) 17. Diet_1t2a-f have been changed to “Number of Showcard 5.__ drinks consumed” 18. New variables added (diet_1t2a_total to diet_1t2f_total) to calculate total in mL: “Amount in mL of Showcard 5.___ drinks consumed:” (**Note. In Redcap, the calculation will be automatic) 19. Section 10: Instruction variable (inst_fpg1) added if fpg_1a=yes 20. Section 10: Variable (inst_fpg1b_opt) added to choose option for reporting FPG. Option 1=mmol/L, Option 2=mg/dL 21. Section 10 : Variable (hba1c_1a_opt) added to choose option for reporting HBA1C. Option 1=percent (%), Option 2=mmol/m   **PART II**   1. Instruction variable (inst_sos1) added at start of Section 13 on how to use Likert scale 2. Text on peer groups and peer leaders removed from start of Section 13 as no longer asking about peer groups/leaders 3. Instruction variable (inst_eff1) added at start of Section 14 on how to use Likert scale 4. Section 14 intro: text “and do physical activity” removed here 5. Section 14 after f: text “maintain a healthy diet and” removed here 6. Instruction variable (inst_aus1) added at start of Section 15 on how to use Likert scale 7. Instruction variable (inst_sreg1) added at start of Section 16 on how to use Likert scale 8. Instruction variable (inst_psa1) added at start of Section 17 on how to use Likert scale 9. Instruction variable (inst_ts1) added at start of Section 18 on how to use Likert scale 10. Section 19: Relabelled and recoded questions L through P to G-K   **PART III:**   1. Instruction variable (inst_oopi1) added at start of Section 21B for referring to the last 3 hospitalizations 2. Section 21B, J-W: New codes for each hospitalization option (e.g. oopi_1k1-3, oopi_1m1-3) 3. Instruction variable (inst_oopi2) added at after question L for reporting hospitalization costs   **SHOWCARDS**   1. Showcard 7 option for Not Applicable changed to 888 |
|  | - Make appropriate changes to translated tools. - This is final version to be administered once questions are clarified. |

INSTRUCTIONS to site teams

- This set of data collection tools contains all the generic instruments that should be used during screening/recruitment and baseline.
- All sections are numbered. Kindly do not change the section numbers, question numbers or codes in this version.
- Please provide laminated SHOWCARDS in colour to all data collectors. Instruct data collectors to give the appropriate SHOWCARD for each section to the participant to make it easier for them to respond.
- It is recommended that baseline data collection is staggered over two occasions to decrease participant fatigue and improve the quality of the data collected. Please follow the recommended steps below to divide the baseline data collection in two steps.
  - **During RECRUITMENT visit**

STEP 1 = Section 1 to confirm eligibility 🡺 Sign informed consent 🡺 Section 2 to assign identifiers 🡺 Sections 2-11.2 🡺 Fill in start date for pedometer reading in Section 11.3 🡺 Give instructions on pedometer use + demonstrate use of pedometer + reset and help the participant to wear a masked pedometer 🡺 Confirm instructions and decide on date to collect back the pedometer after 7 days 🡺 If you are unable to collect back the pedometer after 7 days – give specific instructions on what the participant is expected to do 🡺 BREAK off baseline data collection HERE.

- - **During visit to COLLECT PEDOMETER**

STEP 2 = Meet on previously decided date 🡺 Check pedometer and enter reading and end-date in section 11.3 🡺 Complete sections 12-21. END of BASELINE data collection.

About this document

This is a master document containing the complete set of data collection tools that will be administered using a survey methodology. Please note, that evaluations that involve qualitative methodologies are not included here.

The document is divided into four parts:

*Part I: Basic participant data*

*Part II: Intervention process measures (based on Self Determination Theory)*

*Part III: Selected context measures and expenditure*

*Part IV: Process and fidelity checks*

Please note that this document includes tools pertaining to individuals, facilities and local community. It is not meant to be administered together in one visit. Part I includes the set of tools that should be administered together in one baseline/end-line visit.

Sites have to decide on how to administer parts II and III based on the feasibility of administration. Please take care to include relevant identification information in all sets of questionnaires (particularly, if they are collected during separate visits). Some of the tools can be measured in only a sub-set of the study sample and these have been marked with an * in the tables at the beginning of each part.

